### 4.3. Analysis

The treatment comparison on the difference between the two arms in the changes in brain hippocampal volume at the final visit from baseline will be performed using Repeated-Measures ANOVA.

The test will be conducted at the standard 0.05 significance level. In case of a non-normal distribution, the data will be normalized through a log-transformation. A non-parametric method will be used in case the normality will not be observed after the data transformation.

The treatment effect will be estimated in terms of the difference in changes at the final visit from the baseline between the two treatments, and the corresponding two-sided 95% Confidence Interval (CI) will be provided. All the secondary endpoints will be analyzed according to their standard methods. All the statistical methods will be detailed on the Statistical Analysis Plan which will be finalized before the database freezing. Statistical analysis of the safety data will address the safety population. No method for replacing missing values will be applied, and all the missing datapoints will be removed from analysis according to pairwise exclusion. The MedDRA dictionary will be used for coding AEs. AEs will be summarized by the System Organ Class (SOC) and Primary Preferred Term (PPT). They will also be stratified by seriousness and relationship with the study treatment. All abnormalities noted on the physical examination at enrolment and during this study will be descriptively analyzed as the frequency distribution. Previous and concomitant medications will be coded using the WHO dictionary with the ATC codes. Concomitant diseases at study entry will be coded with the MedDRA dictionary. These data will be descriptively analyzed as frequency distributions.

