Cognitive functions will be evaluated through the administration of the following neuropsychological tests: Mini-Mental State Examination (MMSE); Montreal Cognitive Assessment (MOCA); Memory of the Figure of Rey; Test of Corsi; Verbal Span; Immediate and Deferred Re-enactment of Rey’s 15 words; Free and Cued Selective Reminding Test (FCRST); Clock Drawing Test; Copy of Rey’s Figure; Frontal Assessment Battery (FAB); Phonemic verbal fluency test; Semantic verbal fluency test; Attentive Matrices Test; Beck Depression Inventory (BDI); Apathy Evaluation Scale (AES); Basic Activities of Daily Living (BADL); Instrumental Activities of Daily Living (IADL); and study drug dispensation. The BADL and IADL scales will be administered to the patient’s family member/caregiver.

Baseline Visit (Visit V0) is scheduled within 3 weeks from screening. This visit might overlap with screening if all data requested for enrolment are available. During this visit, the investigator will check for compliance with the inclusion/exclusion criteria. The patients who meet the criteria will be randomized to receive the study treatment (choline alphoscerate or placebo). At the end of the visit, patients meeting the inclusion criteria will be provided with a sealed and coded small box containing the study treatment.

Visit 1 is scheduled at 3 months from baseline visit (±3 days). At this visit, for a compliance check, all used and unused containers of treatment should be returned. The patients will therefore receive choline alphoscerate/placebo for the next 3 months of treatment.

Follow-up will be carried out at 3, 6, 9, and 12 months. The evaluation will be according to the flowchart reported in Figure 1. The patient will perform MRI at enrolment and at 12 months for a detailed measurement of the levels of atrophy in the areas of interest.

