### Randomization

Patients will be randomly assigned to ARM A (placebo) or ARM B (choline alphoscerate) with a 1:1 ratio. The allocation to the assigned treatment ARM will remain unknown to the patients, to the Principal Investigator and/or her delegates, and to the personnel in charge of the data management and the statistical analyses until the database lock. The randomization list will be prepared by an Independent Statistician who will collaborate with the unblended responsible for the preparation of the experimental drug for the randomization list management, using a computer random number generator. The randomization will be performed at Visit 0 (baseline), after the inclusion/exclusion criteria check.

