## 4. Statistical Analysis

### 4.1. Sample Size

In accordance with the primary study objective, the estimation of sample size is based on the variation in the volume of the hippocampus. There is no study evaluating brain atrophy in MCI patients treated with cholinergic drugs. The clinical hypothesis to be verified is a reduction in hippocampal volume. This value has shown the ability to discriminate patients between AD, MCI, and the healthy control [25].

Based on this study, the mean difference in these groups was 0.7 cm^3^ with a maximum standard deviation of 0.6 [25]. Fixing α = 0.05, β = 0.05 (i.e., power = 95%), and SD = 0.6 (chosen as the higher value observed in the reference study) and conducting a two-sided t test, 42 patients (i.e., 21 patients in each arm) are sufficient for detecting a difference of 2 points in MMSE. To reduce the influence of drop-out patients on the estimate of the treatment effect size, a further 25% patients will be added. Based on these calculations, a total of 60 patients (30 in each arm) will be randomized.

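### With MRI at only two times, the planned repeated-measures ANOVA of hippocampal volume is an unadjusted t-test on change; ANCOVA on baseline volume would use data already collected, for a gain that may be small

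*Protocol article*

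**What the plan says.** Section 4.3 (Analysis) describes the primary comparison as "changes in brain hippocampal volume at the final visit from baseline will be performed using Repeated-Measures ANOVA". It names no covariate. The effect is to be reported as the between-arm difference in change, with a two-sided 95% confidence interval. On the error rate it says: "The test will be conducted at the standard 0.05 significance level".

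Section 3 (Trial Design) gives the imaging schedule: "The patient will perform MRI at enrolment and at 12 months". The same section accepts a baseline MRI taken up to 6 months before screening, and puts the baseline visit (V0) within 3 weeks of screening.

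Section 4.1 (Sample Size) rests on a t test: "conducting a two-sided t test, 42 patients (i.e., 21 patients in each arm) are sufficient". Its inputs are given as "the mean difference in these groups was 0.7 cm^3^ with a maximum standard deviation of 0.6", with 95% power. It continues: "a further 25% patients will be added. Based on these calculations, a total of 60 patients (30 in each arm) will be randomized".

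The Randomization subsection describes a computer-generated 1:1 list and mentions no balancing on baseline volume.

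Section 4.3 leaves further detail of methods to a statistical analysis plan, to be finalised before the database is frozen. That plan is not shown.

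**The concern.** The name of the method suggests a longitudinal model, but with two measurement times it reduces to a comparison of mean change between arms. Every patient who contributes a change also has a baseline volume, and the test as named uses it only by subtraction, which fixes the regression slope of follow-up on baseline at 1.

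Two things follow.

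- If the true slope is below 1, some precision is lost.
- If the arms differ at baseline by chance, regression to the mean carries part of that difference into the estimated effect.

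Both deserve attention in a trial of 60 patients whose calculation counts on 42 evaluable. What is at stake is the efficiency of the primary analysis and its robustness to chance imbalance, not its validity.

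**Working it through.** **Inputs.** From the article: two-sided α = 0.05, power 95%, difference 0.7 cm³, SD 0.6 (section 4.1); 1:1 allocation (Randomization); 21 evaluable and 30 randomised per arm (section 4.1); two MRI times and the baseline scan window (section 3). Assumed, because the article gives neither: the correlation ρ between baseline and 12-month volume, shown from 0.5 to 0.98, and equal SDs at the two times.

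**1. The plan's own figure.** With difference 0.7 and SD 0.6, the noncentral t distribution gives 94.9% power at 20 per arm and 95.8% at 21. So 21 per arm (42) is reproduced, and nothing below changes it.

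**2. Equivalence.** With two times, the only within-patient contrast is the change. The arm-by-time F on 1 and 2n − 2 degrees of freedom is therefore the square of the two-sample t on change. In a simulated data set with 21 per arm, F was 1.508011 and t² was 1.508011.

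**3. Precision.** Let s be the common SD. Per patient:

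- change score: 2s²(1 − ρ)
- ANCOVA: s²(1 − ρ²)
- large-sample ratio: (1 + ρ)/2

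Estimating the slope multiplies the ANCOVA variance by 1 + 1/(N − 4), which is 1 + 1/38 at N = 42 and 1 + 1/56 at N = 60. The simulation used 20,000 trials per ρ with 21 per arm.

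| ρ (assumed) | (1 + ρ)/2 | with slope penalty, N = 42 | simulated, N = 42 | with slope penalty, N = 60 |
|---|---|---|---|---|
| 0.5 | 0.75 | 0.77 | 0.78 | 0.76 |
| 0.8 | 0.90 | 0.92 | 0.91 | 0.92 |
| 0.9 | 0.95 | 0.975 | 0.98 | 0.97 |
| 0.95 | 0.975 | 1.00 | 1.00 | 0.99 |
| 0.98 | 0.99 | 1.02 | 1.01 | 1.01 |

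Break-even is at ρ = 2/(1 + 1/38) − 1 = 0.949 for N = 42, and 2/(1 + 1/56) − 1 = 0.965 for N = 60. At ρ = 0.8 the saving of 8 to 9% is worth about 0.08 × 42 = 3.4 to 0.09 × 42 = 3.8 patients.

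**4. A second covariate.** With two covariates the penalty is 1 + 2/(N − 5) = 1 + 2/37 = 1.054 at N = 42. If the second covariate explains nothing, break-even falls to ρ = 2/1.054 − 1 ≈ 0.90. The worst case, with neither covariate informative about change, is a variance about 5% larger in total.

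**5. Chance imbalance.** A one-SE baseline difference at 21 per arm is 0.6 × √(2/21) = 0.185 cm³. Given that difference, the change contrast shifts by (1 − ρ) × 0.185. As a fraction of its own SE the shift is (1 − ρ)/√(2(1 − ρ)) = √((1 − ρ)/2), whatever the SD.

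| ρ (assumed) | shift, cm³ | shift / SE of change contrast |
|---|---|---|
| 0.5 | 0.093 | 0.50 |
| 0.8 | 0.037 | 0.32 |
| 0.9 | 0.019 | 0.22 |
| 0.95 | 0.009 | 0.16 |
| 0.98 | 0.004 | 0.10 |

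**6. Scan interval.** A baseline scan up to 6 months before screening, plus up to 21 days to V0, plus 12 months, puts the scans from about 12 to almost 19 months apart (12 + 6 + 0.7 = 18.7). The inclusion criterion in section 2.2.1 counts the 6 months back from enrolment, which would give about 18. A two-level time factor treats all these intervals as equal.

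**The case against.** The strongest reply is that the planned test has the right size, is unbiased over randomisation, and matches the t test behind the sample size. That stands. Chance imbalance is part of the randomisation error that the confidence interval already covers. That also stands on average over repeated trials, although it does not remove the shift in the one trial that is run.

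The gain cannot be established from the article, because it gives no ρ. If hippocampal volume is very stable over a year, the gain is nil or slightly negative. The ratio (1 + ρ)/2 also needs equal SDs. Covariates are often left to the analysis plan. But the article does name the primary test, so deferral answers the point only in part.

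A reader might infer three stronger points, and the article supports none of them.

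- *That it is unclear which model term decides.* The same simulated data set gave F = 0.103 for the arm main effect, so the terms do differ. But section 4.3 compares the arms on their changes and reports the difference in changes, which identifies the arm-by-time contrast.
- *That MMSE loses every patient with a missed visit, or would gain a large saving.* Section 4.3 assigns repeated-measures ANOVA to hippocampal volume only, names no MMSE model, and states pairwise exclusion of missing data.
- *That ANCOVA is always more precise and free.* Steps 3 and 4 show that it is not.

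**Conclusion.** The point holds as a recommendation. With two MRI times, the named primary analysis is an unadjusted t-test on change, and it makes no further use of a baseline volume that will be in hand. It would be wrong to call it invalid or biased.

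ANCOVA on baseline volume would cut the variance by about 22 to 23% at ρ = 0.5, 8 to 9% at 0.8 and 2 to 3% at 0.9. It would cost at most about 2% at very high ρ. It also removes the shift from chance baseline imbalance, including at high ρ where the precision gain has gone. These figures assume equal SDs, a linear common slope and 21 evaluable patients per arm; ρ is an assumption throughout. The 42 evaluable patients in section 4.1 are unaffected. ANCOVA does not recover patients without a 12-month scan, and baseline volume alone does not correct for unequal scan intervals.

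**What to change.** In section 4.3 and the statistical analysis plan, replace repeated-measures ANOVA for hippocampal volume with an ANCOVA of 12-month volume (or 12-month change; the treatment coefficient is the same) on treatment and baseline volume. Report the treatment coefficient with its two-sided 95% confidence interval as the primary result.

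Consider adding the time from baseline scan to V0 as a second covariate. It is fixed before randomisation and is the main planned source of variation in scan interval. Decide this in advance, not after seeing the fit.

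The cost is one or two degrees of freedom, with the small variance loss shown above if ρ is very high or the interval explains nothing. No new data are needed, and SPSS fits the model. The analysis plan is to be finalised before the database is frozen, so the change can be made while the analysts are blinded. Section 5 sends protocol changes to the ethics committee, so a submission may be needed.

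### The normality-triggered log and rank fallbacks for hippocampal volume do not match the difference in changes with 95% CI that section 4.3 promises in every case

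*Protocol article*

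**What the plan says.** All the operative text is in section 4.3 (Analysis) of the protocol article.

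- **Comparison and test:** the "difference between the two arms in the changes in brain hippocampal volume at the final visit from baseline will be performed using Repeated-Measures ANOVA".
- **First fallback:** "In case of a non-normal distribution, the data will be normalized through a log-transformation". The sentence does not say whether the volumes or the changes are logged.
- **Second fallback:** "A non-parametric method will be used in case the normality will not be observed after the data transformation". The method is not named.
- **Promised estimate:** "The treatment effect will be estimated in terms of the difference in changes at the final visit from the baseline between the two treatments". This is not tied to a branch of the sequence.
- **Promised interval:** "the corresponding two-sided 95% Confidence Interval (CI) will be provided". This is equally unconditional.
- **Deferral:** "All the statistical methods will be detailed on the Statistical Analysis Plan which will be finalized before the database freezing".

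Two other places bear on the point. Section 4.1 gives the expected direction: "The clinical hypothesis to be verified is a reduction in hippocampal volume". Section 3 fixes the measurement times: "The patient will perform MRI at enrolment and at 12 months". There are thus two volumes per patient and one change. Section 2.1.3 ties success to a significant difference from control at 12 months.

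**The concern.** The plan names one effect measure and up to three tests. Which test is used depends on what the outcome distribution looks like. Only the first test, on the original scale, addresses the effect measure that is promised.

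If the fallback is triggered, the trial would report a p-value for one quantity and an estimate with CI for another. Because section 2.1.3 defines success by significance, a p-value and an interval that point different ways would leave the primary conclusion unclear. The remaining choices (which variable to log, which rank method, whether to back-transform) would bear directly on the primary result.

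**Working it through.** The plan gives no figure for the distribution of 12-month change, so there is none to reproduce. The only SD in the document is 0.6 (section 4.1). It comes from a reference study that compares diagnostic groups and is not the SD of a within-patient change. Inputs below marked as assumed are illustrations.

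**Step 1. The untransformed branch is coherent.** With two time points per patient, the arm-by-time test in a Repeated-Measures ANOVA is equivalent to a two-sample t test on the changes. It tests the difference in mean changes, which is the promised estimate.

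**Step 2. Log of the changes.** A log exists only for values above zero. For normally distributed changes with mean m and SD s, the share below zero is Φ(-m/s).

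| Assumed mean (cm³) | Assumed SD (cm³) | Calculation | Share negative |
|---|---|---|---|
| -0.10 | 0.20 | Φ(0.50) | 69% |
| -0.20 | 0.20 | Φ(1.00) | 84% |
| -0.20 | 0.15 | Φ(1.33) | 91% |

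With a mean change of zero the share is 50%, and the chance that all 60 values are positive is 0.5^60, about 9 × 10⁻¹⁹. Analysing loss instead of change only reverses the problem: 100% - 91% = 9% to 100% - 69% = 31% of values would still have no logarithm.

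**Step 3. Log of the volumes.** Volumes are positive, so this can be computed. The arm contrast of log(V12) - log(V0), exponentiated, is a ratio of ratios. Take a loss of 0.1 cm³ on treatment and 0.2 cm³ on control, so that the difference in changes is always 0.1 cm³. At a common baseline b the ratio is (b - 0.1)/(b - 0.2):

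| Assumed baseline (cm³) | Calculation | Ratio of ratios |
|---|---|---|
| 4 | 3.9/3.8 | 1.026 |
| 5 | 4.9/4.8 | 1.021 |
| 6 | 5.9/5.8 | 1.017 |

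One difference in volume corresponds to several ratios, so a result on the log scale has no unique conversion to the promised difference.

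The log need not improve the shape either. A simulation assumed a skewed loss (gamma, shape 1.5, scale 0.1 cm³, less 0.03 cm³) and a baseline of mean 5 and SD 0.6 cm³. Skewness was -1.64 for the raw changes and -1.89 for the changes in log volume.

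**Step 4. Rank test.** A rank test alone gives a p-value. A Hodges-Lehmann estimate would add a shift in cm³ with a CI, but section 4.3 does not name it, and a location shift is not in general the difference in means.

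**Step 5. Raw-scale CI reported beside a fallback test.** A simulation of 4,000 trials used 30 patients per arm, baseline mean 5 and SD 0.6 cm³, mean change -0.15 cm³ on control and -0.10 cm³ on treatment, and change SD 0.10 cm³. Significance at 0.05 differed from the raw-scale analysis in about 7% of trials, both for the rank test and for the log-volume test. The simulated changes were normal, so this shows only that the analyses can conflict. It does not estimate how often they would conflict once the fallback is triggered.

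**The case against.** The strongest reply is that section 4.3 can be read in a workable way. Repeated-Measures ANOVA takes the baseline and 12-month volumes, which are positive and can be logged. The order of the tests is written down in advance. The section headed Randomization keeps the analysts blinded until database lock. The SAP is to be final before the database is frozen, and the transformed variable and the rank estimator are details that a SAP commonly settles. Nothing stops the raw-scale difference and CI from being reported whichever test is used.

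Much of this stands, and it rules out several stronger readings that a reader might infer:

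- **That the log rule cannot be applied at all.** This holds only if the changes are logged. On volumes the rule is computable.
- **That most patients would be lost.** Section 4.3 removes missing datapoints, but it does not say that an observed volume whose transform is undefined counts as missing. Its stated next step after an unsuccessful log is a non-parametric method, which would use all observed patients.
- **That a rank method cannot give an interval.** Hodges-Lehmann does.
- **That the rule would harm the MMSE analysis because of the ceiling at 30.** MMSE appears under the primary endpoint in section 2.1.3, but the sequence follows the hippocampal test and section 4.3 states no MMSE test. The size of any skew would rest wholly on assumed score distributions.

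The deferral to the SAP does not remove the mismatch. The sequence and the promised effect are both fixed in the protocol text, and a SAP that keeps the first still has tests that do not address the second. Blinding limits the scope for choosing a favourable test, but it does not make the test independent of the data.

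**Conclusion.** The concern holds in a limited form. The fallback sequence and the unconditional promise of a difference in changes with a 95% CI are not reconciled under either reading of what is logged, nor under a rank test alone. The mismatch on the log scale is algebraic; the baselines of 4 to 6 cm³ only illustrate it. The 69% to 91% of values without a logarithm applies only if changes are logged, and it rests on an assumed normal distribution with the means and SDs shown. That most changes are negative fits the reduction expected in section 4.1, but the documents give no data on it.

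The consequence is conditional on the normality check failing, and the documents do not show how likely that is. The sample size is not affected. What is at risk is a primary p-value that does not belong to the reported estimate. That deserves correction before the SAP is final.

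**What to change.** Delete the sequence of normality check, log-transformation and non-parametric method for the primary comparison. Replace it with text to this effect:

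> The primary analysis compares the arms on the untransformed change in hippocampal volume from baseline to 12 months. The difference in mean changes, its two-sided 95% CI and the p-value come from the same model, whatever the observed distribution. A Hodges-Lehmann shift estimate with 95% CI is reported as a sensitivity analysis in all cases.

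Inference can be heteroscedasticity-robust (for example HC3) or permutation-based, which is sufficient protection against non-normality at this sample size. One of the two should be named in advance.

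The cost is wording in section 4.3 and the SAP, submission to the Ethics Committee as section 5 requires for protocol changes, and one extra analysis. No additional patients, visits or data are needed.

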#### 2.2.3. Withdrawal Criteria

Patients must be withdrawn under the following circumstances:Patient’s wish to be withdrawn from the study (withdrawal of consent).Patient is lost to follow-up.Major protocol violation considered relevant by the investigator.The protocol therapy may be discontinued if the patient is judged to be intolerant to the study drug.The patient is not able to complete the 12 months’ treatment (<80% compliance).

If, during this study, a full-blown clinical picture of dementia emerges, the patient will be treated with the therapies indicated for this pathology and prematurely discontinued from the study (drop-out) due to disease progression. The data of patients enrolled but not evaluable will, in any case, be collected and entered into the study database. Any discontinuation must be recorded in the case report form by the investigator, who will indicate the date and reason(s) for withdrawal.

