### 4.2. Methods

All the variables will be descriptively analyzed by treatment and visit (mean, median, standard deviation, interquartile range for continuous variables, frequency distribution for categorical variables). Efficacy analysis will be applied in all populations. Results from the ITT (Intention To Treat) population will be considered the primary ones.

Analyses will be performed using SPSS by the Statistician in charge of this study (different from the above-mentioned Independent Statistician). The statistical significance level chosen is equal to 0.05.

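### On the visible text, the primary result labelled ITT is an analysis of patients with both MRI scans, and loss through dementia is tied to the outcome

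*Protocol article*

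**What the plan says.** The relevant statements are spread over several sections of the Protocol article.

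- **Section 2.2.3, Withdrawal Criteria.** The list opens with "Patients must be withdrawn under the following circumstances" and includes "Major protocol violation considered relevant by the investigator". It also covers failure to complete the year of treatment, with an 80% compliance threshold. A separate sentence says that a patient in whom overt dementia emerges will be treated for it and "prematurely discontinued from the study (drop-out) due to disease progression". The section adds: "The data of patients enrolled but not evaluable will, in any case, be collected and entered into the study database".
- **Section 3, Trial Design.** "The patient will perform MRI at enrolment and at 12 months for a detailed measurement of the levels of atrophy in the areas of interest".
- **Section 4.1, Sample Size.** A further 25% of patients are added to limit what drop-outs do to the effect estimate, and 60 are randomised.
- **Section 4.2, Methods.** "Results from the ITT (Intention To Treat) population will be considered the primary ones". The article does not define that population.
- **Section 4.3, Analysis.** The primary comparison is the change in hippocampal volume from baseline to the final visit, by repeated-measures ANOVA. On missing data: "No method for replacing missing values will be applied, and all the missing datapoints will be removed from analysis according to pairwise exclusion".
- **Section 2.1.3, Primary Endpoint.** A 12-month MMSE above that of the control group is also a criterion of success.

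**The concern.** An intention-to-treat result should compare the arms as randomised. Here a patient who leaves before month 12 has one scan and no change score, and the missing-data rule drops that patient from the comparison.

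The loss through dementia is not incidental. The Abstract and Section 6 both tie hippocampal atrophy to conversion from mild impairment to dementia, so the rule removes patients expected to show the most atrophy and the lowest MMSE. If the arms lose such patients at different rates, those who remain are no longer comparable. Bias can then run either way: against the drug if more placebo patients convert and leave, in its favour if more of the worst-progressing patients leave the active arm. A scan that was never taken cannot be recovered by any later analysis plan.

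**Working it through.** **1. What happens to a withdrawn patient.** Section 2.2.3 ends participation in the study, not only in treatment, for a dementia converter. Section 3 gives two scan times. Section 4.3 needs both scans for a change and replaces nothing. Put together, only patients with both scans enter the primary comparison, whatever the population is called.

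**2. What the 25% allowance does.** Inputs from Section 4.1: difference 0.7 cm³, SD 0.6, two-sided α = 0.05, power 95%. The standardised difference is 0.7/0.6 = 1.17. The t test needs 20.1, hence 21 per arm; power at 21 per arm is 95.8%. The stated 42 reproduces. The allowance gives 42 × 1.25 = 52.5 (53 patients) or 42/0.75 = 56; the 60 randomised corresponds to 42/0.70, a 30% loss. That mismatch is a separate matter. What counts here is that extra patients restore the number analysed, and so precision. They do not change which patients are missing.

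**3. Illustrative bias, no true effect, unequal loss.** The article gives no dropout by arm and no strength of link between dropout and atrophy, so every rate below is an assumption. Units are SDs of the change.

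- *Leavers are k SD worse than stayers.* Bias = (p₁ − p₂) × k. With 25% versus 10% and k = 1 to 2: 0.15 × 1 = 0.15 to 0.15 × 2 = 0.30.
- *The worst progressors leave.* Let r be the correlation between dropout tendency and outcome, d the share lost, z the d-quantile of the standard normal and φ its density. The mean of those who stay shifts by r × φ(z)/(1 − d). For r = 1 this is 0.318/0.75 = 0.424 at d = 0.25 and 0.175/0.90 = 0.195 at d = 0.10. The difference is 0.229 for r = 1 and 0.114 for r = 0.5. The sign depends on which arm loses more.
- *Simulated type I error*, 30 per arm, 10,000 runs, same losses: 6.9% (r = 0.5) and 16.4% (r = 1) instead of 5%.

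**4. No true effect, equal loss.** With 25% lost in both arms by the same mechanism, bias is about zero and type I error about 5% (5.3% simulated at r = 0.5).

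**5. A real benefit, one progression cut-off for both arms that removes 25% of controls.**

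| True effect (SD) | Completers, r = 0.5 | Completers, r = 1 |
|---|---|---|
| 0.30 | 0.264 (88%) | 0.173 (58%) |
| 0.50 | 0.446 (89%) | 0.304 (61%) |
| 1.17 | 1.055 (90%) | 0.821 (70%) |

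In this setting the completers' difference understates the benefit.

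**The case against.** The strongest reply is that missing outcomes after withdrawal are inferred rather than stated. Section 2.2.3 promises that data of non-evaluable patients are collected, the visit flowchart in Figure 1 is not shown, and the article condenses a longer protocol. An early-termination scan cannot be ruled out. That stands as a limit on certainty. But entering data in a database is not the same as obtaining or analysing the 12-month outcome, and the text mentions no such scan.

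A second reply is that Section 4.3 defers detail to an analysis plan. That stands for the choice of imputation model. It does not cover the withdrawal rule or the missing-data rule, both of which the article fixes. The missing-data sentence follows one on safety data, but its wording covers all missing datapoints and no other rule is given for efficacy.

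Four stronger readings are tempting and not supported:

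- *That the analysis holds only compliant non-progressors.* Patients who worsen short of overt dementia stay in, as do those whose violations are minor or not judged relevant.
- *That the plan forecasts the loss of 15 of 60 patients.* Section 4.1 states an allowance added to 42, not that forecast.
- *That pairwise exclusion clashes with repeated-measures ANOVA.* With two scans, pairwise and complete-case deletion keep the same patients for a given volume.
- *That randomisation is lost, or that the drug is favoured.* This depends on unequal loss, and the introduction describes side-effects as low and similar to placebo.

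**Conclusion.** The point holds in limited form. On the visible text, the primary ITT result is an analysis of patients with both scans. Loss through dementia is related to the outcome by the article's own account. For low compliance and relevant major violations a link is plausible, but the article does not state one. The enrolment allowance does not address this.

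The direction and size of bias are unknown. About 0.1 to 0.3 SD is an illustration that rests on an assumed 25% versus 10% loss and on assumed links between leaving and outcome. Equal loss with no effect gives about zero. A real benefit would tend to be understated. Confidence is high on what the rules say and moderate on the absence of outcomes after withdrawal. It should be corrected while 12-month outcomes can still be collected.

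**What to change.** 1. In Section 2.2.3, separate stopping study drug from ending data collection. Seek the planned 12-month MRI and MMSE from every randomised patient unless consent is withdrawn or the patient is lost to follow-up. Clinical handling of dementia, intolerance and violations stays as written.
2. In Section 4.2, define ITT as all randomised patients. State how outcomes after a dementia diagnosis and the start of dementia therapy are treated in the primary question.
3. In Section 4.3, replace the rule of no replacement and deletion with an analysis of all randomised patients that is valid under missing at random, such as a mixed model or multiple imputation. The model details can go to the analysis plan. With only two scans, imputation has the advantage that it can use the 6-month cognitive results and the dementia diagnosis.
4. Add a sensitivity analysis for data missing not at random, and report losses by arm and reason.

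The cost is amendment wording, some analysis work and some extra month-12 visits. These lie within the 60 follow-up scans already planned: the design tolerates 60 − 42 = 18 losses, and not all of those could be recovered. The main drawback is that 12-month values in converters will include the effect of other therapy, which is why step 2 must say how they are interpreted.
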